### Instruments

Instruments will be used for the screening process, the clinical outcome assessment and the economic evaluation. In Table 1 an overview of all assessments per time point is shown.

**Table 1 T1:** Overview of instruments per time point

**Instrument**	**Screening**	**Baseline**	**2 months**	**3 months**	**6 months**	**9 months**	**12 months**
Demographic variables	X						
Beck Depression Inventory PC	X						
Composite International Diagnostic Interview		X					
Beck Depression Inventory II		X	X	X	X	X	X
Symptom Checklist 90		X		X			X
Work and Social Adjustment Scale		X		X			X
Dysfunctional Attitudes Scale		X	X	X	X	X	X
WHOQoL-BREF		X		X			X
EuroQol		X		X	X	X	X
Productivity and disease questionnaire		X		X	X	X	X

*Note*. In addition to the regular follow-up measurements, each month the health care use questionnaire will be administered.

#### Beck Depression Inventory for Primary Care

The Beck Depression Inventory for Primary Care (BDI-PC) is a screening instrument for depression consisting of seven items derived from the Beck Depression Inventory II. Each item is assessed at a 4-point Likert-scale (range 0 – 4). Several studies have proven its sound psychometric properties [31,36,37]. A cut-off score of 4 was used in the current study, since this has excellent sensitivity and specificity for identifying a diagnosis of major depression [31].

#### Composite International Diagnostic Interview

To determine in- and exclusion criteria the computerised Composite International Diagnostic Interview (CIDI-auto) will be used. The CIDI is an extensive, fully structured diagnostic interview to assess lifetime and 12-month DSM-III-R diagnoses. The CIDI can be used by lay-interviewers and has acceptable reliability and validity [38,39].

#### Beck Depression Inventory Second Edition

The Beck Depression Inventory II (BDI-II) will be used to measure depressive severity. The total score is the sum of the 21 items with a range of 0 (no depression) to 63 (severe depression). There has been consistent support for the construct validity and reliability of the BDI-II in various samples [40-42].

#### Functional impairment

Functional impairment will be assessed with the SF-36 Health Survey (SF-36), which consists of 36 items measuring 8 multi-item scales. For each subscale items are coded, summed, and transformed on to a scale from 0 (worst possible health state measured by the questionnaire) to 100 (best possible health state). The SF-36 has good psychometric properties in terms of validity, reliability, and scale structure [43-45]. Additionally, the economic evaluation will use the SF-6D utility, which is a quality of life measure derived from the SF-36 [46].

#### Psychological distress

The Symptom Checklist (SCL-90) is a self-report symptom inventory of psychopathology. The SCL-90 consists of 90 items, each rated on a five-point scale of distress from 'not at all' to 'extremely' [47,48]. The total score of the SCL-90 can be used as an index of severity for general psychological distress (score range 90–450) [49]. The SCL-90 has a high degree of reliability and support has been found for the validity [47].

#### Social functioning

The Work and Social Adjustment Scale (WSAS) is a self-report scale of functional impairment attributable to an identified problem. The WSAS consists of five items measured on an 8-point Likert-scale (0 to 8). A high score indicates severe impairment. It has good psychometric properties [50].

#### Dysfunctional attitudes

The Dysfunctional Attitude Scale form A (DAS-A) is a self-report scale designed to measure the presence and intensity of dysfunctional attitudes. The DAS-A consists of 40 items and each item consists of a statement and a 7-point Likert-scale (7 = fully agree; 1 = fully disagree). The higher the score, the more dysfunctional attitudes an individual reports [51].

#### Quality of life measures for the economic evaluation

Measuring health-related quality of life is relevant in patients with depression, since depression has a large impact on the physical, social and emotional aspects that are relevant and important to a patient's well-being [3,4]. An intervention aimed at treating depression is therefore expected to have an impact on the perceived quality of life. In addition, measuring generic quality of life facilitates the comparison of the effects on quality of life of our intervention program with that of other interventions [52]. Quality of life will be measured in three different ways in this study by using the WHOQOL-BREF, the EuroQol and the SF-6D.

The WHOQOL includes a broader range of mental health aspects in its psychological domain compared to other quality of life instruments and is therefore more feasible to use in this study [53]. The WHOQOL-BREF is an abbreviated version of the WHOQOL-100, which has proven to be a valid and reliable alternative [54,55]. The WHOQOL-BREF measures four domains related to quality of life (physical health, psychological health, social relationships and environment) and includes two questions on overall quality of life and general health [55].

Generic quality of life will be derived by means of the EQ-5D of the EuroQol group. The EQ-5D consists of five health state dimensions (mobility, self-care, usual activity, pain/discomfort and anxiety/depression) on which the respondent has to indicate his own health state [56,57]. The EuroQol will be assessed since it is a validated and widely used quality of life instrument, both nationally and internationally [58]. An advantage of the EuroQol is that it is short and that an overall utility score for population-based quality of life can be obtained, which facilitates comparisons with other interventions and health states in other disease areas. A utility refers to the preference that individuals or society may have for any particular set of health outcomes. It is indicated by a number between 0 (the worst imaginable condition: death) and 1 (perfect health) [52]. Standardised value sets are available to calculate the utility based on the EQ-5D. This study will use the Dutch tariff and the original UK tariff to value generic quality of life [58-60]. The utility scores of the EQ-5D will be used to calculate the quality adjusted life year (QALY) during the follow-up period by adjusting the length of time affected through the health outcome by the utility value [52].

An adapted version of the EuroQol is the EQ-5D+C, in which a sixth domain (cognitive functions referring to memory, concentration, coherence and IQ-level) is added to the five existing domains of the EQ-5D [61-63]. This sixth domain of the EQ-5D+C is also included in the questionnaire to provide additional information on quality of life. However, since there is no tariff developed to compute utility scores for the EQ-5D+C, utility scores and QALYs will only be calculated based on the five domains of the EQ-5D.

The SF-6D is a utility instrument based on the health-related quality of life questionnaire SF-36. The utility score is derived from 11 items of the SF-36 and is composed of six dimensions of health (physical functioning, role limitations, social functioning, pain, mental health, and vitality). The SF-6D utilities will be derived by means of the preference-based UK tariff [46].

#### Costs

Costs will be defined from the societal perspective. Within our study we distinguish three cost-categories: health care sector costs, costs for the patient and family, and productivity costs [52].

A health care use questionnaire will be developed to measure the psychological, paramedical, medical, paid and informal care, participation in a self-help group, and alternative treatments received by the patient on a monthly base. This health care use questionnaire will be based on an existing cost diary [64] and retrospective cost questionnaires [65,66], and is adapted to depressive patients. This questionnaire will provide information to calculate health care sector costs by measuring the volume of care provided, and out-of-pocket expenses, which are part of the costs for the patient and family. The other part of the patient and family costs will concern costs of travelling and lost time due to the primary care intervention TAU and/or CCBT. The time spent by a patient on CCBT will be tracked by means of the computer-registered login and logout data of the program. In the health care use questionnaire the duration of a GP consult will be registered by the patient. The number of GP consults informs on the number of travels from/to the GP, and will be linked to average distances from/to a GP. Dutch guideline prices will be used to value the costs of the health care items [67]. If for specific cost-categories cost guidelines are unavailable, average tariffs or shadow prices will be used. The standard cost prices and tariffs of health care practitioners include the integral costs, being all costs directly and indirectly attributable to the cost unit.

For the measurement of production losses, the patient modules B, C, D and E of the PROductivity and DISease Questionnaire (PRODISQ) will be used [68,69]. These modules consist of questions concerning the profession, working situation, income, absence from work, compensation mechanisms in case of absence for paid work and productivity costs at work (efficiency loss) of the patient. Productivity costs will be calculated according to the friction cost approach [67,70], using one general cost price per lost hour of productivity [67]

### Analyses

#### Clinical analyses

Data-analysis will include intention-to-treat analysis and per-protocol analysis. Analysis will include elementary head-to-head comparisons of the intervention groups as well as more complicated multi-level analysis incorporating patients and time measurements if necessary. An integrity check and a process evaluation will be performed using qualitative methods of analysis. In case of missing data, we will impute intermittent missing data using the mean of the values of a previous and a subsequent time point. Other missing data (i.e. missing values due to lost to follow-up) will only be imputed when more then 15% of the data are missing.

To test the main hypotheses, difference scores for all outcome variables will be calculated (t_0 _minus t_k_) and compared between the three groups using ANOVA. In case of violation of assumptions, robust ANOVA can used [71]. We will then compute improvement effect sizes and between-group effect sizes [72] or robust equivalents [see [73]]. Next, we will calculate the number of patients who showed reliable and clinically significant change on the BDI-II using the method of Jacobson and Truax [74]. This calculation is based on two components: (1) the extent to which the pre-to-post-difference score is reliable taking into account the measurement variability of the instrument (reliable change; RC), and (2) the extent to which post-treatments scores are clinically meaningful (clinically significant change; CSC) [75]. Chi-square tests will be used to test the frequency differences in RC, CSC and RC+CSC between the three groups.

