### Current study

In the present study we aim to evaluate the (cost-) effectiveness of online CCBT for mild to moderate depression in primary care. In a randomised trial we will compare (a) CCBT with (b) treatment as usual (TAU) by a GP, and (c) CCBT in combination with TAU. In a recent Dutch study of Spek et al. (2007), the same CCBT program has shown to be equally effective as group CBT in people over 50 years old with subthreshold depression [28]. Based on the results from a recent systematic review [23] we hypothesise that CCBT will be more effective than TAU by a GP. Furthermore, we hypothesise that CCBT in combination with TAU will be more effective than CCBT alone by increasing treatment adherence. Although some studies have shown that for mild depression a combination of pharmacotherapy and psychotherapy does not appear more effective than psychotherapy alone [29], other studies suggested that patients receiving combined treatments were more likely to stay in treatment and comply to the treatment protocol [30].

Regarding the economic evaluation we hypothesise the following. The self-help intervention CCBT alone implies costs of time spent by the patient on the treatment and costs of the development of the program, while the TAU treatment requires costs related to a GP consult and/or medication. We hypothesise that from a societal perspective, these costs of the intervention CCBT are comparable to the costs of the intervention TAU. However, as a consequence of our hypothesis that CCBT is more effective than TAU, we expect that CCBT will be more preventive in health care use and productivity loss during the follow-up period, and thus result in lower costs compared with TAU by a GP. As a consequence of the expected increase of effectiveness (in terms of depression and quality of life) and decrease of costs, we hypothesise that CCBT is more cost-effective than TAU by a GP. Hypotheses about the intervention CCBT in combination with TAU are that it is both more costly and more effective compared with stand alone CCBT or TAU.

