### Interventions

The CCBT program (named "colour-your-life") is an online, multimedia, interactive, self-help computer program for depression, and was developed by Riper and Kramer (2004) [32] of the Trimbos-institute (the Netherlands Institute of Mental Health and Addiction). The program is based on the principles of CBT and on the Dutch version of the 'coping with depression course' of Lewinsohn [33,34]. The program consists of eight weekly 30-minute sessions and a ninth booster session, although the duration of sessions can vary among users. At the end of each session homework-assignments are given, such as keeping a 'mood diary'. Patients allocated to the intervention CCBT or the combination CCBT and TAU will be given log in codes by the researchers at inclusion and they will access the program at home. No professional assistance will be offered. The program was originally developed for people over 50-years old [28] and is adapted for an adult population (18 to 65 years) for the current study. GP's of patients allocated to CCBT only will be informed about the participation and treatment allocation of their patient.

In the TAU and CCBT&TAU group, participants will be advised to contact their own GP. GPs of patients in the TAU and the CCBT&TAU group will be sent a letter, informing them about their patients' study participation, and advising them to follow the depression guideline as described by the Dutch College of General Practitioners [35]. This guideline states that treatment should formally consist of four to five biweekly consultations over the course of nine weeks in combination with antidepressant treatment if indicated. In case of suicidal risk, social dysfunction, symptom deterioration or non-improvement in six to twelve weeks time, referral to specialist mental health care settings is recommended. In practice however, usual care is whatever the GP prescribes.

An integrity check will be performed to assess treatment quality and protocol compliance using computer records of the CCBT program and questionnaires assessing use of GP and other health care (i.e. health care use questionnaire).

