### Why do we need more research on CCBT in primary care?

There are several reasons why we are conducting this study. First, the only study so far on CCBT in primary care used a program that was delivered on a computer in the general practice [26]. Since the Internet can increase the accessibility of such an intervention, we will offer the CCBT program on the Internet. In the Netherlands, almost all of the general adult population has access to Internet, and this will only increase in the next decade [84]. Second, in the only other study on CCBT in primary care [26], a nurse provided practical support at the start and end of each session. We will study the effectiveness of CCBT as a pure self-help intervention; no support or guidance will be given to the patient. Third, the effects of a combined treatment (i.e. both CCBT and treatment as usual by a GP) still need to be evaluated. We think this might have extra effects in terms of improvement in depressive severity and quality of life. Although the GP is not directly involved in the CCBT program, a combined treatment might also increase adherence to the intervention. Previous studies already showed that minimal therapist contact could increase the adherence to Internet-based interventions [85,86], a result which was recently confirmed in a meta-analysis [87]. Next to that, the GP can monitor the progress of the patient and can pay attention to non-verbal signals of the patient. Finally, only one study so far has conducted an economic evaluation of CCBT [27].

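### The combination arm is hypothesised to work by raising adherence to CCBT, but the one analysis described for compliance is fixed as qualitative and no between-arm comparison of adherence is described (minor)

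*Protocol article*

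**What the plan says.** - **Hypothesis.** Under Current study the authors write: "we hypothesise that CCBT in combination with TAU will be more effective than CCBT alone by increasing treatment adherence". The Discussion repeats the idea more cautiously, saying that "a combined treatment might also increase adherence to the intervention", and adds other ways the GP might help, namely monitoring progress and noticing non-verbal signals.
- **Where compliance is assessed.** Under Interventions: "An integrity check will be performed to assess treatment quality and protocol compliance using computer records of the CCBT program", together with the health care use questionnaires.
- **How that check is analysed.** Under Clinical analyses: "An integrity check and a process evaluation will be performed using qualitative methods of analysis".
- **How the hypotheses are tested.** The same section says: "To test the main hypotheses, difference scores for all outcome variables will be calculated". These are baseline minus follow-up, compared across the three groups by ANOVA. Adherence is not among the instruments in Table 1.
- **What usage data exist.** Under Costs: "The time spent by a patient on CCBT will be tracked by means of the computer-registered login and logout data of the program". The use given for these data there is the costing of patients' time.
- **Other uses of compliance.** Per-protocol analyses are foreseen in both the clinical and the economic sections.

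**The concern.** The hypothesis for the third arm has two parts: that the combination reduces depression more than CCBT alone, and that it does so through better adherence. The first part has a test. For the second, the article names a method, and a qualitative one cannot estimate whether adherence differs between two randomised arms or attach an error rate to the answer.

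What is at stake is the interpretation of CCBT versus CCBT&TAU. If the arms do not differ on the BDI-II, readers will want to know whether GP care failed to raise adherence or whether higher adherence brought no benefit. If the combination does better, the result alone cannot separate adherence from the other GP effects that the Discussion names. A quantitative comparison of use would resolve much of the first question and inform the second, and the article says that usage data are recorded by the program.

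**Working it through.** **1. Does any described analysis compare adherence between the two CCBT arms?**

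| Described analysis | Uses compliance or usage data? | Compares adherence between CCBT and CCBT&TAU? |
|---|---|---|
| ANOVA on difference scores | No; needs a baseline value, and use of the program has none | No |
| Reliable and clinically significant change, chi-square | No; BDI-II only | No |
| Integrity check and process evaluation | Yes | Not quantitatively; method stated as qualitative |
| Per-protocol analyses | Yes, to define who is analysed | No |
| Patient time costs | Yes, login time is priced | Not described; it enters cumulative cost per patient |

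No row supplies a between-arm test of adherence.

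**2. Would a quantitative comparison be informative at the planned size?**

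The article gives no figure for adherence, so there is none to reproduce. From Sample size I take 100 per group and alpha 0.05; how the 100 was derived does not matter here. Two-sided testing is my assumption, since sidedness is not stated.

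*Continuous measure (time logged in, or sessions).* Detectable standardised difference = (z for alpha/2 + z for power) × √(2/n).
- 80% power: (1.960 + 0.842) × √(2/100) = 2.802 × 0.1414 = 0.396, about 0.40.
- 90% power: (1.960 + 1.282) × 0.1414 = 0.458, about 0.46.

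*Binary measure (course completed or not).* With p the mean of p1 and p2, power = Φ{[(p2 − p1) − 1.96 × √(2p(1 − p)/n)] / √[p1(1 − p1)/n + p2(1 − p2)/n]}.

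Example, 40% versus 60%: the null standard error is √(2 × 0.25/100) = 0.0707 and the alternative standard error is √(0.48/100) = 0.0693. Then (0.200 − 1.96 × 0.0707)/0.0693 = 0.886, and Φ(0.886) = 0.812.

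The completion rates below are assumptions; the article gives none.

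| CCBT-alone rate | +10 points | +15 points | +20 points |
|---|---|---|---|
| 20% | 37% | 66% | 88% |
| 30% | 32% | 59% | 83% |
| 40% | 29% | 57% | 81% |
| 50% | 29% | 57% | 83% |

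**3. Sensitivity to incomplete records.** Program records need not be lost when a patient stops filling in questionnaires, but the article does not say that they are complete. If only 100 × 0.8 = 80 per arm were usable, the detectable standardised difference at 80% power would be 2.802 × √(2/80) = 0.443, and power for a 20-point rise would fall to 72–79%.

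**The case against.** The strongest reply is that this is a condensed article. An adherence comparison or a mediation analysis may sit in the full protocol or the analysis plan, neither of which is shown. That stands against one tempting inference, that the mechanism is never tested: the article cannot establish this. It does not remove the point, because the article is not silent. It names a method for the compliance check, and that method does not fit the hypothesis.

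A reader might also infer that compliance data are used only in the qualitative check. That is not so. The per-protocol analyses need a classification of patients by compliance, and login time enters the cost analysis as a number. Neither compares adherence between arms, however: the first defines a population and the second prices time.

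Third, the adherence clause can be read as rationale rather than as something to be tested, and the Discussion wording is softer. This has some force. The effectiveness claim is one of the two comparisons in the sample size section, and it is tested. The article also nowhere commits itself to crediting a positive result to adherence.

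Fourth, the word qualitative may be loose drafting that covers the integrity check and the process evaluation together, since the check draws on numeric sources. If so, the correction is a clarification of one sentence.

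Finally, the article mentions login and logout times and otherwise unspecified computer records. It does not say that sessions completed are logged, and time logged in is not the same thing. The choice of measure has to allow for this.

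**Conclusion.** The point holds in a limited form. Half of the stated hypothesis, that adding GP care raises adherence, has no between-arm test described, and the method fixed for the only described assessment of compliance is unsuited to one. The other half, superiority on depression severity, is tested as planned. The primary outcome, the randomised comparisons and the economic base case are unaffected, so this is a cheap improvement to a secondary analysis.

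A quantitative comparison would be informative for moderate differences and weak for small ones. Small ones are plausible, because combination patients are only advised to contact their GP, who has no direct part in the program. These figures rest on 100 analysable patients per arm, two-sided alpha 0.05, assumed completion rates and, for the continuous measure, a normal approximation that is rough if many patients never log in.

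**What to change.** In Clinical analyses, confine qualitative methods to the rest of the process evaluation. For use of the CCBT program, prespecify a secondary comparison of CCBT versus CCBT&TAU:

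- **Population:** all patients randomised to either arm, with those who never log in counted as zero.
- **Measure:** time logged in, which the Costs section says is recorded; or sessions completed, if the program records hold it. Choose one before outcome data are seen, and measure it over the same period in both arms.
- **Reporting:** the between-arm difference with a confidence interval, labelled secondary.
- **Interpretation:** state that this tests whether adding GP care raises adherence. It does not test whether adherence mediates the BDI-II effect; that claim would need a separate mediation analysis with its own assumptions.

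If the full protocol or analysis plan already contains such a comparison, aligning the sentence on qualitative methods with it is enough.

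The cost is about one paragraph and, if login time is used, no new data collection. The downside is one more secondary comparison, with low power for small differences, so a non-significant result should not be read as showing equal adherence.

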**Methods/Design:**

In a randomised trial we will compare (a) computerised cognitive behavioural therapy with (b) treatment as usual by a GP, and (c) computerised cognitive behavioural therapy in combination with usual GP care. Three hundred mild to moderately depressed patients (aged 18–65) will be recruited in the general population by means of a large-scale Internet-based screening (*N *= 200,000). Patients will be randomly allocated to one of the three treatment groups. Primary outcome measure of the clinical evaluation is the severity of depression. Other outcomes include psychological distress, social functioning, and dysfunctional beliefs. The economic evaluation will be performed from a societal perspective, in which all costs will be related to clinical effectiveness and health-related quality of life. All outcome assessments will take place on the Internet at baseline, two, three, six, nine, and twelve months. Costs are measured on a monthly basis. A time horizon of one year will be used without long-term extrapolation of either costs or quality of life.

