### Sample size

Power calculations are based on elementary head-to-head comparisons of CCBT versus usual care and CCBT versus the combined treatment (t-test). A clinically relevant treatment effect is derived from the only study of CCBT in primary care [26]. For a mean difference in change scores of 5 (SD 5.25) on the BDI-II, a sample size of 84 participants per group is needed (power 90%, alpha 0.05). Adjusting for potential study withdrawal (20%), we estimate that 100 participants per group are needed.

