#### Economic evaluation

Since the follow-up period lasts one year and no extrapolation over time will be executed, discounting of costs is not necessary. All costs will be indexed to the year 2007 by means of the price indexes of the Dutch Central Bureau of Statistics (CBS).

For each patient, volumes of care, travels, lost time for receiving care and lost productivity hours will be multiplied by the prices determined for each cost item. Based on the costs per item, costs during the follow-up period will be calculated as the cumulative costs per patient. The costs at baseline and during the follow-up period of the three groups will be compared by the non-parametric bootstrapping method with confidence intervals in percentiles. By bootstrapping, samples of the same size as the original data are drawn with replacement from the observed data [76]. The quality of life and clinical outcome variables will be compared between the three groups at baseline and during the follow-up period using ANOVA.

In case of baseline differences of costs, effectiveness, or utility scores between the patient groups, corrections will be performed [77-79]. The economic evaluation will consist of a base-case cost-effectiveness and cost-utility analysis, and sensitivity analyses. Uncertainty of parameter estimates of the base-cases will be dealt with by these sensitivity analyses [52]. In the base-cases, data will be analysed according to the intention-to-treat principle. Incremental cost-effectiveness ratios (ICERs) will be determined on the basis of incremental costs and incremental effects [52] of (a) stand alone CCBT compared with (b) usual GP care, or (c) a combination of CCBT and usual GP care. The primary outcome measure for the cost-effectiveness analysis is depression measured by the BDI-II, and for the cost-utility analysis the QALY based on the EQ-5D. The cost-effectiveness ratio will be stated in terms of costs per point improvement on the BDI-II, the cost-utility ratio will focus on the net cost per QALY gained. In our primary analysis QALYs will be derived from the EQ-5D using the UK-tariff. Scores on the quality of life domains derived from the WHOQOL-BREF and the sixth domain of the EQ-5D+C will be used to provide in-depth insight into the quality-of-life.

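### The 15% imputation trigger makes the main ANOVA a completer analysis when missingness is low, against the stated intention-to-treat principle, and the neighbour-mean rule is badly weighted at month 2

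*Protocol article*

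**What the plan says.** Under Clinical analyses, the protocol article states: "Data-analysis will include intention-to-treat analysis and per-protocol analysis". The Economic evaluation section, where the BDI-II is the effect measure of the cost-effectiveness analysis, repeats the principle: "In the base-cases, data will be analysed according to the intention-to-treat principle".

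Missing values are handled by two rules under Clinical analyses. For gaps between attended visits: "we will impute intermittent missing data using the mean of the values of a previous and a subsequent time point". For dropout: "Other missing data (i.e. missing values due to lost to follow-up) will only be imputed when more then 15% of the data are missing". The denominator of the 15% is not given.

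The main hypotheses are tested on difference scores, baseline minus visit k, which are "compared between the three groups using ANOVA". A model that could use incomplete records appears only as an option: "more complicated multi-level analysis incorporating patients and time measurements if necessary". No role in missing data is stated for it.

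The visits are unequally spaced: "All outcome assessments will take place on the Internet at baseline, two, three, six, nine, and twelve months". Table 1 shows the BDI-II at all of them. The Sample size section makes an allowance for loss: "Adjusting for potential study withdrawal (20%), we estimate that 100 participants per group are needed".

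**The concern.** A patient with no value at visit k has no difference score and cannot enter the ANOVA for that visit. When 15% or less is missing, nothing replaces the value, so the named main test uses completers only while the text promises intention to treat. Whether dropouts are in or out is settled by which side of a threshold the observed data fall.

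This matters more here than in many trials. The Current study section expects GP care to raise adherence over CCBT alone, and the Interventions section offers CCBT users no professional assistance. Adherence to treatment is not the same as staying in the study, but unequal loss between arms is foreseeable.

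The rule for intermittent gaps is a second weakness. An equal-weight mean ignores the visit spacing, and at month 2, about the end of the eight weekly sessions, one of the two neighbours is baseline. The ANOVA then treats filled-in values as observed.

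**Working it through.** The plan gives no computed figure on this point, so its rules are checked directly.

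**1. Which branch applies.** Read the 15% as patients out of 300 (an assumption): 0.15 × 300 = 45, so imputation starts at 46 losses. With independent losses, the binomial chance of 46 or more is:
- true dropout 15%: 0.46
- true dropout 20% (the planned allowance, 60 patients): 0.98

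Near the threshold the analysed set is close to a coin toss. At the planned rate the imputation branch is almost certain.

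**2. Completer bias in the no-imputation branch.** Let p be the dropout share in an arm and d the amount by which completers improve more than dropouts. The completer mean exceeds the full mean by p·d, so the bias of the contrast is p_A·d_A − p_B·d_B. The protocol supplies neither p by arm nor d; the values below are assumed.

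| Dropout A / B | d_A / d_B | Bias (points) |
|---|---|---|
| 15% / 15% | 5 / 5 | 0.75 − 0.75 = 0 |
| 20% / 10% | 2 / 2 | 0.40 − 0.20 = 0.2 |
| 20% / 10% | 8 / 8 | 1.60 − 0.80 = 0.8 |
| 15% / 15% | 5 / 0 | 0.75 − 0 = 0.75 |

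**3. Simulation, true 12-month difference 5.** Assumed: SD 10, correlation 0.6 between all visits, 100 per arm, loss after month 3 driven by change from baseline to month 3.
- Same dropout and same mechanism in both arms: completers 5.0.
- About 24% against 7% lost, same mechanism: 5.6.
- About 24% against 7% lost, mechanism in one arm only: 5.9.
- About 15.6% lost in each arm, opposite mechanisms: 6.2.

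Predicting month 12 from the observed earlier scores returns 5.0 in every case. With a true difference of 0, the completer type I error is about 0.05 when dropout and mechanism match, and 0.06, 0.10 and 0.15 in the three unequal cases.

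In the 24% against 7% cases, a third arm that also loses 7% gives (24 + 7 + 7)/3 = 12.7% overall, below 15%. The last case stays at or below 15% only if the third arm loses no more than 45 − 2 × 15.6 = 13.8%.

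A second set-up assumed SD 7 at baseline and 10 later, correlations 0.4 and 0.7, CCBT loss of 23–25% rising with month-2 BDI-II, and 8% lost in each other arm (13–14% overall). It gave 5.4 to 6.2 in completers and 5.0 using earlier scores.

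One result limits the point. In the first set-up, when loss depended on the month-3 score itself rather than on change, completers gave 5.0 even with unequal dropout. With equal correlations between visits, the score at month 3 carries no information on change from baseline to month 12.

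**4. Neighbour mean.** Linear-in-time weight on the previous visit, against 1/2 under the rule:
- month 2: (3 − 2)/(3 − 0) = 1/3
- month 3: (6 − 3)/(6 − 2) = 3/4
- month 6: (9 − 6)/(9 − 3) = 1/2
- month 9: (12 − 9)/(12 − 6) = 1/2

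Month 12 has no later visit, so the rule cannot apply there. At month 2 the imputed contrast is (0 + month-3 contrast)/2, because randomisation makes the expected baseline contrast 0. If the 5-point effect is complete by month 2 and persists, this is 2.5 instead of 5. With a share m of month-2 values filled in each arm, the contrast falls by 2.5·m: 0.13 at m = 5% and 0.50 at m = 20%. On the same assumption month 3 is unaffected. If the effect instead grows linearly to 5 at month 3 and then stays flat, a filled month-2 value carries 2.5 instead of 3.33, and a filled month-3 value carries (3.33 + 5)/2 = 4.17 instead of 5.

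**The case against.** The strongest reply is that the plan expects 20% loss, where imputation applies with about 98% probability and the intention-to-treat conflict does not arise. That stands as a limit on how likely the completer branch is. It does not rescue the rule: the 20% is an allowance for possible withdrawal, and better retention would move the trial into the branch that drops patients.

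A reader might infer that the rule does bias the BDI-II result. The documents do not support that. They give no dropout by arm and no mechanism, and the bias is zero when both match. The figures of 5.4 to 6.2 are illustrations under chosen inputs.

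A reader might also take the 15% as pooled over arms, so that heavy loss in one arm could hide below it. The text does not say. Read per arm, a 24% loss in CCBT would trigger imputation there, and the illustrations with unequal loss would not apply as they stand.

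Nor can it be said that dropout is left unhandled. The multi-level analysis is available as an option, the imputation method above 15% may be set out in a fuller plan and is not counted as a fault, and the Randomisation and procedure section limits gaps with email alerts, reminders and phone calls.

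On the neighbour mean, the objection that the effect is small and local is right: it matches linear interpolation at months 6 and 9, and month 2 is not named as the primary time point.

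**Conclusion.** The point holds in a limited form. At 15% missing or less, the main test as written is a completer analysis, in conflict with the intention-to-treat statement under Clinical analyses, and with the one under Economic evaluation if the same BDI-II handling carries over. A data-dependent threshold decides who is analysed. This part needs no assumed dropout figures.

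Bias is possible, not shown. It requires dropout, or its relation to earlier scores, to differ by arm, and dropout to be related to change. In the illustrations it reaches about 0.4 to 1.2 points on a true difference of 5. These rest on assumed SDs, correlations and arm-specific losses.

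The neighbour mean is a smaller defect, chiefly at month 2: about 0.13 to 0.50 points if 5 to 20% of values are filled and the 5-point effect is complete by then. Treating filled-in values as observed understates uncertainty, but the size of that was not calculated. It would be wrong to add the two effects together, since the dropout illustration concerns month 12 and the neighbour mean concerns month 2.

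**What to change.** Delete the 15% trigger and the neighbour-mean rule. Make the multi-level (mixed) model already named under Clinical analyses the primary intention-to-treat analysis at any missing rate, using all observed BDI-II values with baseline, visit and treatment-by-visit terms. Where a complete value per patient is needed, as for reliable and clinically significant change, use multiple imputation. Add one sensitivity analysis under a missing-not-at-random assumption.

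The cost is a change of wording before the data are seen and modest extra analysis work; data collection is unchanged. The model assumes missing at random given the observed scores. That is weaker than what a completer analysis needs, but it is still an assumption, which is why the sensitivity analysis belongs in the plan.
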